All procedures will be performed under general anaesthesia using a supraglottic airway device. Anaesthesia will be induced with i.v. propofol (2–4 mg kg^−1^) and sufentanil (0.2 μg kg^−1^), and maintained with sevoflurane (1–3%). Metronidazole (1 g), dexamethasone (8 mg), and droperidol (0.625–1.25 mg) will be administered unless contraindicated. The pudendal nerve block will be performed under general anaesthesia with the patient in the lithotomy position. Patients will be randomly assigned (1:1) to the neurostimulation-guided or ultrasound-guided group.•In the neurostimulation group, after antiseptic preparation, a 22 G, 50 or 80 mm insulated needle (Stimuplex Ultra 360, BBraun, Melsungen, Germany) will be inserted at the midpoint between the anus and the ischial tuberosity, connected to a stimulator (Stimuplex HNS12, BBraun). Electrical stimulation will begin at 2.5 mA with a frequency of 1 Hz. The needle will be advanced to a depth of 4–5 cm until a contraction of the anal sphincter is observed. Once a response is obtained, the current will be reduced to 0.5 mA to confirm appropriate needle placement. If no response is observed, current intensity will be temporarily increased. A strong response at <0.3 mA will prompt repositioning to avoid intraneural injection. After negative aspiration, ropivacaine 15 ml (3.5 mg ml^−1^) will be injected incrementally. The procedure will be repeated contralaterally. If no response is obtained, the block will be performed blindly at a depth of 4 cm.•In the ultrasound group, after antiseptic preparation, a 6 MHz convex probe will be placed transversely on the perineum, between the anus and the ischial tuberosity. The pudendal artery will be identified near the ischial tuberosity. A 22 G, 50 or 80 mm echogenic needle (Ultraplex 360, BBraun, Melsungen, Germany) will be inserted out-of-plane in the area on the medial side of the artery. After negative aspiration, ropivacaine 15 ml (3.5 mg ml^−1^) will be injected slowly. The spread is expected within the ischiorectal fossa. The procedure will then be repeated on the contralateral side.

Block fidelity will be assessed by visualisation of local anaesthetic spread adjacent to the pudendal artery in the ultrasound group, and by the minimal stimulation current eliciting anal sphincter contraction in the neurostimulation group. All investigators were trained and had each performed at least 10 procedures with each technique before trial initiation.

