Postoperative analgesic management is standardised, with systematic administration of paracetamol, ketoprofen, and nefopam, and the use of opioid analgesics if pain control is insufficient.

The primary outcome is the maximum pain score in the PACU before opioid administration, assessed using a 0–10 NRS. The NRS was chosen as it is the standardised measure of pain intensity routinely used in the PACUs of all participating centres. Given the variability in length of stay in ambulatory haemorrhoid surgery, more complex or delayed assessments (e.g. repeated measures, early quality of recovery score [QoR-15] ) would carry a higher risk of missing data. The NRS thus provides a simple, robust, and homogenous endpoint across centres. Secondary outcomes include opioid consumption in PACU (converted to i.v. morphine equivalents), nerve block duration, block procedure time, pain scores at rest and during movement at 24 h, 3 and 7 days, total analgesic use over 7 days, timing and pain intensity of first defecation, PACU and hospital stay durations, and adverse events (e.g. sciatic nerve block, haematoma, vascular puncture, rectal injury). Functional recovery will be evaluated with the QoR-15 score on postoperative days 1, 3, and 5.

All adverse events will be documented from randomisation until postoperative day 7 through direct questioning, medical record review, and nursing reports. Each event will be graded (mild, moderate, severe) and assessed for causality (unrelated, possible, probable, definite). Serious adverse events will be reported to the sponsor within 24 h in accordance with French regulations. Based on institutional data (mean pain score 3.4 [2.0]), a non-inferiority margin of 0.7, standard deviation of 2.0, 80% power and one-sided α=0.05, a sample size of 101 patients per group is required. Thus, 202 patients will be enrolled.

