Based on preliminary data (mean NRS 3.4 [2.0]), a total of 202 patients (101 per group) is required to test non-inferiority, standard deviation of 2.0, one-sided alpha of 0.05, and 80% power. The non-inferiority margin was set at 0.7 NRS points (20% of the expected mean score), as smaller differences were not clinically relevant and larger ones were considered unacceptable. As the trial follows the intention-to-treat principle, crossovers will be analysed; if patients withdraw consent before surgery, replacements will be recruited to reach 202 participants. A detailed statistical analysis plan will be finalised before database lock. The primary outcome—maximum pain score in the PACU—will be compared using Student’s *t*-test or the Wilcoxon rank-sum test. Secondary outcomes (e.g. opioid use, pain trajectories, QoR-15, length of stay, block duration) will be analysed using appropriate parametric or non-parametric tests. Repeated measures will be assessed via analysis of covariance (ancova), with baseline pain as a covariate. As postoperative pain variability between these procedures was smaller than interindividual variability in our preliminary study, they will be analysed together; however, exploratory subgroup analyses by surgical technique will be conducted if sample sizes allow. Missing data will not be imputed, but patterns and extent of missingness will be described. Sensitivity analyses may be performed if appropriate. Adverse events will be summarised by severity and relationship to the intervention.

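### The primary PACU pain comparison is unadjusted although baseline pain is already a planned covariate; if that score is taken before the block, adjusting for it is an optional gain in precision

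*Protocol article*

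**What the plan says.** All the analysis statements are in the protocol article under Data collection, management, and analysis. The primary outcome "will be compared using Student’s *t*-test or the Wilcoxon rank-sum test". No covariate is attached to that comparison. Shortly afterwards the same paragraph says: "Repeated measures will be assessed via analysis of covariance (ancova), with baseline pain as a covariate". The other secondary outcomes are given suitable parametric or non-parametric tests, again with no covariate named.

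The endpoint itself is defined under Participants, interventions, and outcomes: "The primary outcome is the maximum pain score in the PACU before opioid administration, assessed using a 0–10 NRS". It is one value per patient. The outcome list there has pain scores in the PACU, at 24 hours, on days 3 and 7 and at first defecation. It does not list a preoperative pain score, and the article does not say when baseline pain is recorded.

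The sample size rests on a margin of 0.7 and "standard deviation of 2.0, one-sided alpha of 0.05, and 80% power", from which "a total of 202 patients (101 per group) is required to test non-inferiority". Further detail is left to a statistical analysis plan to be finalised before database lock.

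**The concern.** A pain score taken before treatment is a natural covariate for a pain score taken after it. By naming baseline pain for the repeated measures, the plan indicates that it expects the score to be prognostic and intends to have it. The primary endpoint is also a postoperative pain score, and it is the only analysis with a margin and a stated power, yet it is compared without the covariate and no reason is given.

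What is at stake is the width of the confidence interval set against 0.7. In a randomised comparison of means, linear adjustment for a pre-treatment score leaves the mean difference being estimated unchanged. It removes the part of the outcome variance that the baseline score explains and corrects for chance imbalance in that score between the arms.

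**Working it through.** **Inputs from the article.** Margin 0.7; SD 2.0; one-sided alpha 0.05 (z = 1.645); 80% power (z = 0.842); 1:1 allocation; 101 per group. The calculation takes a true difference of 0.

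**Input not in the article.** The correlation r between baseline pain and maximum PACU pain. It is treated as an assumption and shown over a range.

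**Step 1: reproduce the plan's figure.** n per group = 2 × [2.0 × (1.645 + 0.842) / 0.7]² = 100.94, rounded up to 101, or 202 in total. This agrees with the article.

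**Step 2: power of the planned unadjusted test.** The standard error is 2.0 × √(2/101) = 0.281. Power = Φ(0.7/0.281 − 1.645) = 80.0% (79.8% with the noncentral t distribution). The design meets its own target.

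**Step 3: power with ANCOVA.** The residual SD becomes 2.0 × √(1 − r²), and power = Φ(0.7 / [2.0 × √(1 − r²) × √(2/101)] − 1.645).

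| Assumed r | Residual SD | Power at 101 per group | n per group for 80% |
|---|---|---|---|
| 0 | 2.000 | 80.0% | 101 |
| 0.1 | 1.990 | 80.4% | 100 |
| 0.2 | 1.960 | 81.4% | 97 |
| 0.3 | 1.908 | 83.2% | 92 |
| 0.4 | 1.833 | 85.7% | 85 |
| 0.5 | 1.732 | 89.0% | 76 |

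The gain is 1.4 percentage points at r = 0.2, 3.2 at 0.3, 5.7 at 0.4 and 9.0 at 0.5. It passes 2 points only above about r = 0.25.

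**Step 4: effect of missing baseline scores.** The article rules out imputation, and 202 carries no allowance for missing data. Let a fraction m of baseline scores be missing, unrelated to arm or outcome.

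- If those patients are dropped, the variance relative to the unadjusted analysis is (1 − r²)/(1 − m). This equals 1 when m = r², so the gain is cancelled at 1% missing (about 2 of 202 patients) for r = 0.1 and at 4% (about 8 patients) for r = 0.2.
- If those patients are kept, with the overall baseline mean filled in for the covariate only, the relative variance is about 1 − r²(1 − m), which does not exceed 1.
- Example with r = 0.3 and m = 10%: dropping gives 0.91/0.90 = 1.01, slightly worse than no adjustment. Keeping gives 1 − 0.09 × 0.90 = 0.919.

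**The case against.** The strongest case against is that nothing here is wrong. The sample size uses the unadjusted SD and the test is unadjusted, so they match, and under 1:1 randomisation without stratification the test is valid. One value per patient and a repeated series can properly be analysed by different methods. All of that stands. A reader might infer that the trial loses power against its 80% target; Step 2 shows that it does not. A reader might also infer that baseline pain is used in every analysis but the primary. The article names it for the repeated measures only.

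The second objection is that baseline pain is undefined. Since no preoperative score is listed as an outcome, baseline for the later series could mean a PACU score. Such a score is measured after the block, and leaving it out of the primary would then be correct. This stands as a condition, and the fix meets it by restricting the covariate to a pre-block score.

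The third is that the gain rests on a correlation nobody has reported, and that it may be low for pain measured after a bilateral block and surgery in patients without chronic opioid-treated pain. This also stands, and it is why the gain can only be given as a range.

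The fourth is that covariates belong in the analysis plan, which is not shown and may already contain an adjusted analysis. This carries less weight, because the article itself states the primary method and attaches the covariate only elsewhere. An analysis plan that follows this text would carry the unadjusted test forward.

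**Conclusion.** The point holds as an optional improvement. The planned primary comparison is valid and delivers the stated 80% power. It forgoes precision that adjustment for a pre-block pain score could supply, with the same mean-difference estimand. For correlations from 0.1 to 0.5, power would rise from 80.0% to between 80.4% and 89.0%. The rise is negligible at 0.2 or below and becomes material at about 0.4.

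This rests on three assumptions that the article does not settle: that baseline pain is scored before the block, that it is nearly complete or its gaps are handled without dropping patients, and that it correlates appreciably with PACU pain. It would be tempting to say that adjustment can never do harm. The documents do not support that, because with no imputation a few missing baseline scores would cancel a small gain, as Step 4 shows.

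**What to change.** Under Data collection, management, and analysis, and in the statistical analysis plan:

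- Define baseline pain as the NRS recorded before the block.
- State that the primary between-arm mean difference and its one-sided 95% confidence limit, to be set against 0.7, come from a linear model (ANCOVA) of maximum PACU NRS on arm and baseline pain.
- Keep the unadjusted difference as a sensitivity analysis.
- Keep patients with a missing baseline score in the model by a simple arm-blind rule, such as mean imputation of the baseline covariate only, and word this as an exception to the no-imputation statement. The outcome itself stays unimputed.
- If baseline pain proves to be a PACU or other post-block score, do not use it as a covariate for the primary analysis.

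The change should be fixed before any outcome data are seen by arm. It needs no extra patients and only a change of wording if the pre-block score is already collected. If it is not in the eCRF, the cost is one additional question before surgery, and anyone enrolled before that question is added would have no value and fall under the missing-baseline rule.

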### Participants, interventions, and outcomes

This trial will be conducted in three private hospitals in France: Hôpital Privé Claude Galien (Quincy-sous-Sénart), Clinique des Côtes du Rhône (Roussillon), and Groupe Hospitalier Diaconesses Croix Saint-Simon (Paris). All centres are equipped with ambulatory surgical facilities and PACUs. The trial will take place in operating theatres and postoperative recovery areas. Participants will be recruited from patients scheduled for outpatient haemorrhoid surgery. Eligibility screening will be performed during preoperative anaesthesia consultations. Study information sheets and oral explanations will be provided at this time, and written informed consent will be obtained before surgery. Randomisation will occur on the day of surgery, and participants will receive either an ultrasound-guided or neurostimulation-guided bilateral pudendal nerve block before the procedure. Recruitment is expected to be completed within 12 months.

Inclusion criteria are adult patients (≥18 yr) undergoing outpatient haemorrhoid surgery under general anaesthesia who provide written informed consent (including pedicular haemorrhoidectomy, stapled haemorrhoidopexy, or haemorrhoidal artery ligation with mucopexy). Exclusion criteria include prior haemorrhoid surgery, contraindication to study medications, spinal anaesthesia, contraindication to the use of a supraglottic airway device, chronic pain requiring opioids, cognitive or language impairments, lack of affiliation with the French health system, legal protection status, pregnancy or inadequate contraception, and participation in another clinical trial.

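### The primary comparison leaves out surgical technique and centre, and the reason given for pooling three operations does not justify this; the test stays valid, but precision and protection against chance imbalance are lost

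*Protocol article*

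**What the plan says.** All references are to the protocol article.

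- **Population.** Participants, interventions, and outcomes admits several operations, "including pedicular haemorrhoidectomy, stapled haemorrhoidopexy, or haemorrhoidal artery ligation with mucopexy", at three hospitals.
- **Randomisation.** The same section sets the ratio: "Patients will be randomly assigned (1:1) to the neurostimulation-guided or ultrasound-guided group". Assignment of interventions describes permuted blocks and states that nothing is stratified, so neither technique nor centre is balanced by design.
- **Primary analysis.** Data collection, management, and analysis names Student's t-test or the Wilcoxon rank-sum test for maximum pain in the PACU. Neither has a covariate.
- **Reason for pooling.** "As postoperative pain variability between these procedures was smaller than interindividual variability in our preliminary study, they will be analysed together". No figures by operation are given. Technique appears only in exploratory subgroups, and only if numbers permit.
- **Adjustment elsewhere.** Repeated measures are to be analysed by ANCOVA, "with baseline pain as a covariate". The article does not say when baseline pain is measured.
- **Sample size.** "Based on preliminary data (mean NRS 3.4 [2.0]), a total of 202 patients (101 per group) is required to test non-inferiority", with "standard deviation of 2.0, one-sided alpha of 0.05, and 80% power" and a margin of 0.7.

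**The concern.** A prognostic factor can be worth adjusting for even when it explains much less variance than the differences between patients do; most useful covariates are of that kind. The comparison the article makes therefore cannot settle whether technique should be in the model. Read as a statement about variances, it only says that technique explains less than half of the total.

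Technique and centre are controlled neither by the randomisation nor by the primary test. At stake is some avoidable noise in the estimate, and an estimate left uncorrected if the arms happen to differ in their mix of operations. With a margin of 0.7 points and planned power of 80%, modest gains in precision are worth having when they need no extra patients.

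**Working it through.** **Inputs from the article.** Margin 0.7, SD 2.0, one-sided α 0.05, power 80%, 1:1 allocation, 101 per group.

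**Assumed.** True difference 0 (not stated, but it reproduces the plan's N). SD 2.0 is the total SD with operations pooled. R², the share of variance explained by technique and centre, is not in the article, so a range is shown.

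**1. The plan's own figure.** n per group = 2 × 2.0² × (1.645 + 0.842)² / 0.7² = 100.94, rounded up to 101, or 202 in total. This agrees with the article. Power at 101 per group is 80.0% by the normal approximation and 79.8% by the noncentral t.

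**2. What the pooling reason allows.** Take three equally common operations (assumed) and total variance 4.
- Means at −1, 0 and +1 around the average: between-operation variance 2/3, within 4 − 2/3 = 3.33, ratio 0.20, R² 0.17.
- Means at −1.5, 0 and +1.5: between 1.5, within 2.5, ratio 0.60, R² 0.375.

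Both satisfy the article's criterion, although the operations differ by 2 or 3 NRS points. These are illustrations of what the criterion permits, not estimates.

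**3. Power with adjustment.** Residual SD = 2.0 × √(1 − R²); SE = residual SD × √(2/101).

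| R² (assumed) | Residual SD | Power, normal | Power, noncentral t |
|---|---|---|---|
| 0 | 2.00 | 80.0% | 79.8% |
| 0.02 | 1.98 | 80.7% | 80.5% |
| 0.05 | 1.95 | 81.8% | 81.5% |
| 0.10 | 1.90 | 83.6% | 83.3% |
| 0.20 | 1.79 | 87.2% | 87.0% |

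The model has a price. Technique and centre add four parameters, and chance correlation with treatment inflates the variance by about 1 + 4/(202 − 4 − 3) = 1.02. At R² 0.02 the net factor is 0.98 × 1.02 = 1.00, so the gain is cancelled. With 196 degrees of freedom, net power is 79.8%, 80.9%, 82.7% and 86.4% at R² 0.02, 0.05, 0.10 and 0.20.

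**4. Chance imbalance.** The SD of the shift it causes is 2.0 × √R² × √(2/101).
- R² 0.05: 0.063, so 95% of randomisations lie within ±0.12.
- R² 0.20: 0.126, so ±0.25.

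A concrete case is an operation with 30% prevalence and a 1.5-point difference in pain (both assumed). Then √(2 × 0.3 × 0.7/101) = 0.0645, times 1.5 = 0.097, times 1.96 = ±0.19.

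This is part of the ordinary standard error, 2.0 × √(2/101) = 0.281. Its share of the sampling variance is 0.097²/0.281² = 12%.

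**5. Consequence within one randomisation.** Let s be a shift of 1 SD.
- False non-inferiority after a favourable shift = 1 − Φ((1.645 × 0.281 − s)/residual SE). At R² 0.20: 1 − Φ((0.463 − 0.126)/0.252) = 9.0%. At R² 0.05: 7.2%.
- Power after an unfavourable shift = Φ((0.7 − s − 0.463)/residual SE), which is 67% at R² 0.20 and 74% at R² 0.05.

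Averaged over all randomisations the error stays nominal: a simulation of 20,000 trials at R² of about 0.2 gave 5.1%.

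**The case against.** The strongest reply is that this is a preference for efficiency, not an error. A comparison of randomised groups needs no covariates to be valid, the sample size reproduces, and the type I error is kept. That stands in full. A reader might infer that pooling biases the comparison or makes 202 too few; the article supports neither.

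A reader might also take the ±0.19 shift as a threat on top of the stated power. It is not: the SD of 2.0 already contains the variation between operations, so the planned power and the confidence limit already allow for it. Only the conditional argument in step 5 survives.

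The magnitudes are assumed, and that also stands. The only evidence in the article is that variation between operations was the smaller component. At the low end of R² the gain is one or two points or, after the cost of the extra terms, nothing.

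The pooling sentence can fairly be read as justifying joint study rather than denying prognostic value. On that reading it is unobjectionable, but it then gives no reason to omit technique from the model.

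Lastly, the statistical analysis plan is not at hand and may add adjusted supportive analyses. That does not remove the point, because the article itself fixes the primary test and gives the reason for pooling.

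**Conclusion.** The point holds as one of efficiency and conditional protection, not of validity. The pooling reason does not support an analysis blind to technique, and neither technique nor centre is handled by design or by the primary test.

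The gain from adjusting is probably modest: about 1 to 2 power points at R² 0.02–0.05, 3 to 4 at 0.10 and 7 at 0.20, each reduced by about 0.6 to 0.7 points for the added terms. These figures rest on assumed R², a true difference of 0 and SD 2.0 as the pooled total. The preliminary data by operation would settle the size.

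One further inference should be resisted: that baseline pain is a ready covariate for the primary outcome. The article names it for repeated measures only and does not show that it is measured before randomisation.

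**What to change.** Before database lock, prespecify as primary analysis a linear model of maximum PACU NRS on treatment, planned surgical technique and centre. Compare the one-sided 95% upper limit of the adjusted mean difference (ultrasound minus neurostimulation) with 0.7.

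- Use the technique planned and recorded before randomisation. The block precedes surgery, so the operation actually done is settled only after allocation.
- Add baseline pain only if it is measured before randomisation.
- Keep the unadjusted difference as a sensitivity analysis.
- Treat technique subgroups or a treatment-by-technique interaction as descriptive; with three operations among 202 patients they will be imprecise.

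The cost is four degrees of freedom and about 2% in variance, no extra patients, and a small change to a published primary analysis. Planned technique must be on record before randomisation. Ethics and dissemination requires prior ethics committee approval of substantial amendments, so the sponsor should check whether this change counts as one.

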### Monitoring

No formal data monitoring committee has been established for this trial, given the low-risk nature of the interventions and short-term follow-up. Trial oversight will be ensured by the sponsor through regular on-site and remote monitoring visits, as outlined in the monitoring plan. These visits will verify protocol compliance, data quality, and participant safety, following standard sponsor procedures and applicable regulatory requirements. No interim analyses or formal stopping rules are planned. Safety data will be continuously reviewed by the sponsor’s study team, who may suspend or terminate the trial if unexpected serious safety concerns arise.

